### Procedures

A written consent will be obtained from each participant at the beginning of the study. The investigators will remain available by phone or e-mail during the study duration to answer any question.

#### Screening

During the first telephone contact with the interested participants, they will be informed of the protocol and study design. If interested, one of the two main investigators (CG or NM) will ensure that participants meet all the inclusion criteria. If eligible, they will have to watch the information video and confirm their choice of intervention. Once a group is almost complete (i.e., around 10 participants), the first evaluation (T0) will be scheduled.

#### Measurement Points (T0, T1, T2, and T3)

Each of these four measurement points will be completed by every participant and will consist of several questionnaires (at T0, T1, T2, and T3) and neurobiological measures (at T0, T1, and T3; see Table 1). Questionnaires will be completed online at home, on a secured website.^2^ For those who do not have a computer or are not comfortable using one, it will be possible to make an appointment with one of the investigators to complete the questionnaires with them. At each measurement point, the risk of missing responses is very low, as the online questionnaires are designed in a way that does not allow for missing answers. The investigators will check before the first group session that all participants have answered the questionnaires and remind them if it is not done. For the participants who will complete the questionnaires with one of the investigators, all answers will be checked to minimize missing data.

The neurophysiological and biological measures will be collected at the hospital (CHU of Liège), during a session of ±1 h (see point 3.6.). Tumor marker rates will be collected directly from the patient’s medical record or by asking them to send us their last blood test result. All data will be anonymized: a code will be attributed to each participant and used during the entire study. Only the researchers involved in this study will have access to the final datasets. Review of the trial process and difficulties encountered are discussed regularly between the researchers involved.

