**Diary of practice** (frequency, details about some intense episodes, feelings, impressions, etc.)			X			
**Hypnosis/meditation/SICT and imaginary experience**: •VAS (/10): expectations, motivation to experience hypnosis/meditation/SICT^*^ •Personal definition and *a priori* according to the chosen intervention (free text)^*^ •CEQ		X				
**Quality of life-related variables**: •Fatigue and sleep: MFI20 and ISI •Emotional distress: HADS •Pain: VAS (/10) •Self-reported cognitive functioning: FACT-Cog v3 •Other psychological variables: MAC, CERQ, MPFI-24, Empowerment [7 VAS (/10)], major life events		X		X	X	X
**Neurophysiological and biological variables**: •EEG resting state		X		X		X
•EEG during hypnosis, meditation or SICT state^*^				X		X
•ECG, EMG, and respiration (effort and pressure)		X		X		X
•Core body temperature		X		X		X
•Tumor marker rates		X		X		X
**Questionnaires about the intervention**: •Free recall of a hypnosis/meditation/SICT/intense autobiographical episode (written, according to the intervention) •MCQ •MEQ30 •Presence questionnaire •VAS (/10): Quality of the relationship with the therapist^*^				X	X	X

BFI, Big Five Inventory; CEQ, Creative Experiences Questionnaire; CERQ, Cognitive Emotion Regulation Questionnaire; FACT-Cog, Functional Assessment of Cancer Therapy – Cognitive Function; HADS, Hospital Anxiety and Depression Scale; ISI, Insomnia Severity Index; MAC, Mental Adjustment to Cancer Scale; MCQ-30, Memory Characteristics Questionnaire; MEQ30, Revised Mystical Experience Questionnaire; MFI-20, Multidimensional Fatigue Inventory; MPFI-24, Multidimensional Psychological Flexibility Index; ECG, electrocardiogram; EEG, electroencephalogram; EMG, electromyogram; VAS, Visual Analogue Scale.

* Only for the participants in one of the 3 intervention groups.

Each participant from the three intervention groups will be evaluated before the intervention (T0), right after the last group session (T1), at 3 months (T2) and 1 year (T3) post-intervention. Participants in the control group will be evaluated according to a similar schedule (see Figure 1 for study design, and sections “Procedures” and “Assessments” for more information on procedures and measurements). The first intervention group (hypnosis) started in April 2021.

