### Eligibility

Inclusion criteria will be: to be at least 18 years old, no psychiatric or neurological disorders, no current and regular practice of hypnosis, meditation or trance, diagnosis of cancer (any localization except brain tumors to avoid any effect on EEG data or severe cognitive impairments that could prevent filling the questionnaires adequately), and completion of active treatments (surgery, chemotherapy, radiotherapy) for less than a year. Interested patients will be screened for fatigue, emotional distress, sleep difficulties, and pain (VAS score ≥ 4/10 for one of these four symptoms for inclusion), based on recommendations from our past studies (Grégoire et al., 2018a,b).

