
#### Neurophysiological and Biological Measures

We will record an electroencephalogram (EEG) resting state (256 EGI, Geodesics) during 15 min, combined (T1 and T3) or not (T0) with an EEG during hypnosis, meditation, or SICT state (15 min). During each EEG, we will also record an electrocardiogram (ECG) and an electromyogram (EMG), and measure the breathing (effort and pressure, Polygraph Input Box of EGI system) and body temperature. Tumor marker rates (according to the patient’s diagnosis) will also be collected in the patient’s medical record or based on their blood test results.

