### Statistical Analyses

Baseline (T0) demographic, medical, and psychological data will be compared between groups to test for initial groups equivalency using inferential statistics, including ANOVAs and chi-square tests. Normality of data will be checked using Shapiro–Wilk test. Group-by time changes, and pre- and post-assessment comparison of each variable within each group will be assessed using repeated measures MANOVA followed by post hoc comparisons, on the participants who completed all the needed assessments points. Hierarchical linear regressions will be conducted to investigate the factors associated with the evolution of our main outcomes. All tests will be two-tailed, and the alpha will be set at 0.05. For EEG data analysis, MATLAB, EEGLAB, FieldTrip, Brainstorm, and in-house MATLAB and Python modules will be used. EEG signal will be preprocessed as in our previous works [downsampling, epoching, filtering, removing noise (notably using ICA), channels interpolation, re-referencing; Carrière et al., 2020; Thibaut et al., 2021]. EEG markers will then be extracted: spectral (e.g., power spectrum density), connectivity (e.g., weighted symmetrical mutual information), complexity (e.g., permutation entropy; Engemann et al., 2018). We will also apply graph theory connectivity measures to further assess changes between brain regions (Chennu et al., 2017; Carrière et al., 2020; Thibaut et al., 2021). Results will be corrected for multiple comparisons and considered significant at *p* < 0.05. Statistical analyses will be performed after all data have been collected for T2, then for T3 and T4.

All participants will be informed by e-mail about the final results of the study. Scientific publications and presentations will also be planned.

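### Tumor markers scheduled at T0, T1 and T3 come from the patient's record or last blood test, so the T1 value may predate the end of the intervention or repeat the T0 sample, with a chance that differs by arm

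*Protocol article*

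**What the plan says.** Table 1 lists "Tumor marker rates" among the neurophysiological and biological variables and marks them at T0, T1 and T3. The section Measurement Points gives the same timing for the "neurobiological measures (at T0, T1, and T3; see Table 1").

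That section says the neurophysiological and biological measures are taken in a hospital session of about one hour, but then gives the markers a different source: either the medical record or the patients themselves, "by asking them to send us their last blood test result". The section Neurophysiological and Biological Measures agrees and adds that the marker varies between patients: "Tumor marker rates (according to the patient’s diagnosis) will also be collected in the patient’s medical record or based on their blood test results". Under Eligibility, the cancer may be of "any localization except brain tumors".

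The Design section places T1 right after the last group session and T3 one year after the intervention. Statistical Analyses states that group-by-time changes and "pre- and post-assessment comparison of each variable within each group will be assessed using repeated measures MANOVA", on participants who completed all the needed assessment points. It sets out separate methods for EEG but none for tumor markers.

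**The concern.** A pre/post comparison needs one value from before the intervention and one from after it. A last available result guarantees neither. When it is requested right after the final session, it will usually have been drawn before that session. It may also be the sample already entered at T0, in which case the recorded change is zero whatever happened to the patient.

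The chance of this depends on the time from T0 to T1, which is shorter in SICT than in the two eight-week courses. Apparent stability at T1, or a difference between arms, could therefore come from the timing of blood tests. A repeated old sample would also count as a completed assessment, so restricting the analysis to completers would not remove it.

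A second, smaller issue is scale. Markers chosen by diagnosis need not share units or reference ranges. Arms are chosen by the patient, so the mix of cancers may differ between them.

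**Working it through.** The article gives no figure for this point, so there is none to reproduce. Its sample size does not rest on the markers.

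**Step 1: does the T1 value follow the intervention?** This needs no assumption about testing frequency. T1 is right after the last session, and the value is the last result or a record entry. Unless blood happens to be taken around the visit, or a later record entry is used, the sample predates the end of the intervention. The article has no rule selecting such a later entry.

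**Step 2: minimum time from T0 to T1, by arm.**
- SICT has two 2-day workshops two weeks apart (section Self-Induced Cognitive Trance). From first to last day this is 14 + 2 = 16 days if the two weeks run from start to start, or 2 + 14 + 2 = 18 days if they run from end to start. The working value is 2.5 weeks.
- Hypnosis and meditation have eight weekly sessions (Design), so seven intervals, or 7 weeks. With T0 up to a week before the first session this is 8 weeks.
- Control follows a similar schedule, but its gap is not given, so no share is computed.

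**Step 3: chance that no new sample is drawn between T0 and T1.** The article gives no testing interval. Assume tests at a regular interval of L weeks, at a random phase relative to T0. With a gap of g weeks, the share with no new test is max(0, 1 − g/L). For SICT and L = 13, this is 1 − 2.5/13 = 0.81.

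| Assumed interval L | SICT (g = 2.5) | Eight-week courses (g = 7 to 8) |
|---|---|---|
| 4 weeks | 38% | 0% |
| 8 weeks | 69% | 0% to 12% |
| 13 weeks | 81% | 38% to 46% |
| 26 weeks | 90% | 69% to 73% |

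**Step 4: scheduling slack.** The gaps in step 2 are minimums. T0 is scheduled once a group of around 10 is almost complete, and each patient needs a hospital session. If slack adds 2 to 4 weeks (an assumption), the SICT gap is 4.5 to 6.5 weeks. At L = 13 the share falls from 81% to between 1 − 4.5/13 = 65% and 1 − 6.5/13 = 50%.

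**Step 5: T3.** T1 to T3 is about 52 weeks. The formula gives 0% for any interval up to 52 weeks, so reuse is a problem of T0 to T1 only.

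**Step 6: different markers under one heading.** Eligibility admits all cancers but brain tumors, the marker follows the diagnosis, and Table 1 has one row for markers. Read literally, the analysis sentence covers that row and would place unlike quantities in one repeated measures MANOVA. The article does not state that this will be done.

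**The case against.** The strongest reply is that this is a journal article. Draw dates, visit windows and a rule against reusing a sample are details that a full protocol or data form would hold, and their absence here would be no finding. That stands for the window as such. It does not answer step 1: the article states the source of the value, and that source, followed as written, does not deliver the post-intervention value that Table 1 schedules.

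A second reply is that the size is assumed. This also stands. The documents give no testing interval and do not say that blood is taken only at routine follow-up. A reader might infer that the T0 to T1 change is zero by construction for many patients. The documents do not support that: with tests every 4 weeks, reuse vanishes in the eight-week courses, and slack lowers it in SICT.

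A third reply concerns pooling. A reader might infer that raw values of different markers will be averaged together. The article never says so. The analysis wording is generic, and the article itself notes that the marker depends on the diagnosis. What remains is an ambiguity to close.

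Finally, markers are not among the primary outcomes or the named secondary examples, and no hypothesis in the Discussion mentions them. That limits the severity.

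**Conclusion.** The point holds for the T0 to T1 comparison. The stated source can return the T0 sample again at T1, or one drawn before the intervention ended, and the chance of reuse differs by arm because the gaps differ. Under assumed regular testing every 4 to 26 weeks and minimum gaps, reuse ranges from about 38% to 90% in SICT and 0% to 73% in the eight-week courses. These figures show the possible range and are not estimates for this trial. They fall with scheduling slack and with more frequent testing.

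It would be wrong to extend the reuse problem to T3, about a year later. The concern about unlike markers rests on a literal reading of one sentence and is a matter of clarification.

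Severity is low. The main conclusions do not depend on the markers. The risk is a misleading side result, since Table 1 groups them with the biological variables and following neurobiological correlates over time is a stated aim.

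**What to change.** - Record with each value the draw date, marker name, unit and laboratory upper limit.
- Count a result for a visit only if it was drawn after the previous visit and within a fixed window of the current one. Otherwise set it to missing. Never use one sample for two visits.
- Keep T1 values that meet the window. Dropping T1 markers altogether is not needed.
- Analyse within patient on the same marker, for example as the log ratio to the patient's own T0 value or as a multiple of the laboratory upper limit. Report descriptively, and state that raw marker values stay out of the MANOVA.

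The cost is a few fields on the data form and one or two sentences in the analysis section, with no added burden for patients. Where source results carry a draw date, the rule can also be applied to patients already enrolled. The downside is fewer usable marker values, mainly at T1.

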### Interventions

#### Hypnosis

This intervention will include eight 2h weekly sessions in groups of approximately 10 participants. This protocol has been developed and will be led by one of the authors ([name]), who is an anesthesiologist and an international expert in hypnosis. A large part of the first session will be devoted to answering to the participants’ questions and giving information about hypnosis. First exercises will be proposed as introduction to hypnosis: a focused listening of different musical records and some imagery exercises. The aim is for the participants to notice their abilities to access mental imagery and hypnosis. During the other sessions, a debriefing of at-home practice will be proposed, along with different hypnosis exercises. They will be repeated and discussed, and participants will also attempt to induce hypnosis by themselves during the last session. Table 2 summarizes the exercises that will be done at each session. Between sessions, participants will be encouraged to practice the different exercises at home with the help of audio recordings of the hypnosis exercises. This is essential to take full advantage of hypnosis without the help of a therapist. A self-care approach will be fostered during the intervention, more specifically during the debriefings of the participants’ practice, if they encounter difficulties or ruminations. Concrete strategies to deal with such difficulties will be proposed by the therapist. The importance to take time for themselves will be emphasized, as well as to allow themselves to take a break from their routine and practice hypnosis in their daily life to improve their wellbeing, in an adaptation of our usual practice with oncological patients in clinical and experimental settings (Charland-Verville et al., 2017; Grégoire et al., 2018b, 2020a).

**Table 2 tab2:** Summary of the content of the sessions for each intervention.

	Hypnosis	MSC meditation		Self-induced cognitive trance (SICT)
Session 1	Explanations about hypnosis and answers to questions. Exercises based on focused listening of musical records specially composed by a certified music therapist, and mental imagery.	Explanations about meditation and answers to questions. Exercises based on the discovery of mindful self-compassion (soothing touch, self-compassion break).	Workshop 1—Day 1	Explanations about SICT and answers to questions. SICT exercises using sound loops. Individual search of one or several movements or sounds to induce SICT without listening to the sound loops. Debriefing of each exercise in group. Focus on the transformative power of SICT (i.e., impact on bodily sensations and somatosensory processes, on cognition and emotions).
Session 2	Discussion of self-care strategies in accordance to the difficulties encountered by the participants. Soothing White Clouds exercises.	Mindful self-compassion exercises (affectionate breathing, grounding, mindfulness in daily life, present moment).		
Session 3	Discussion of self-care strategies in accordance to the difficulties encountered by the participants. Safe Place exercises.	Benevolent love exercises (affectionate breathing, love for a close one, self-compassion, and benevolent love).	Workshop 1—Day 2	SICT exercises using different sound loops and individual movements or sounds. Debriefing of each exercise in group. Focus on the transformative power of SICT.
Session 4	Discussion of self-care strategies in accordance to the difficulties encountered by the participants. Garden of dreams exercises.	Discovery of one’s compassionate voice exercises (self-compassion, security and self-criticism, self-compassionate letter).		
Session 5	Discussion of self-care strategies in accordance to the difficulties encountered by the participants. Pain and Colors exercises.	Importance of living intensely (giving and receiving compassion, personal values and wishes, silver lining, compassionate listening).	Workshop 2—Day 1	Debriefing of the 2-week individual practice. SICT exercises using different sound loops and individual movements or sounds. Debriefing of each exercise in group. Consolidation of the participants’ self-induction ability. Focus on the interactions during SICT (i.e., with the environment).
Between sessions 5 and 6	/	Half a day of silent intensive practice (review and deepening of all the exercises previously worked on)		
Session 6	Discussion of self-care strategies in accordance to the difficulties encountered by the participants. Glove Analgesia exercises.	Dealing with difficult emotions [self-compassion, acceptation and management of emotions, “soften, soothe, allow” (basic and specific to shame)].		
Session 7	Discussion of self-care strategies in accordance to the difficulties encountered by the participants. Levitation exercises.	Exploration of difficult relationships (compassionate friend, unfulfilled needs, Qi gong, self-compassion break in relationships, compassion with equanimity, dealing with compassion fatigue).	Workshop 2—Day 2	Debriefing of the 2-week individual practice. SICT exercises using different sound loops and individual movements or sounds. Debriefing of each exercise in group. Consolidation of the participants’ self-induction ability. Focus on the interactions during SICT.
Session 8	Discussion of self-care strategies in accordance to the difficulties encountered by the participants. Stories and Metaphors exercises.	Embracing life (self-compassion and compassion for others, appreciation and gratitude, self-compassion bracelets).		
Each session	Debriefing of the previous session and at-home practice.			

#### MSC Meditation

This intervention will include eight sessions of 2 h45 in groups of approximately 10 participants. It will be led by two of the authors ([name] and [name]), recognized as experts in MSC meditation. The intervention is based on the practice of MSC meditation, already described above. At the beginning of the first session, a presentation of the intervention will be proposed along with explanations about meditation and answers to participants’ questions. Each session will focus on a theme, linked to self-compassion (see Table 2), and will be based on formal practices (e.g., guided meditation), experiential exercises, informal practices linked to the daily life and theoretical information about compassion and emotions. Each exercise will be debriefed in small or large groups, in order to allow each participant to share their feelings, thoughts and questions. Between each session, individual practice will be encouraged and audio recordings of different exercises will be given to the participants.^3^ Between the fifth and the sixth session, half a day of silent intensive practice will be organized, during which all the exercises previously worked on will be reviewed and deepened.

#### Self-Induced Cognitive Trance

This intervention will include two 2-day workshops, spaced by two weeks, in groups of approximately 10 participants. A part of the first session will be devoted to explain what is SICT, how it can be accessed and how the workshops will take place. Possible questions among the participants will be discussed. To induce SICT, different sound loops (i.e., electronic designed sounds, voices, and noises, inspired by the ones produced during traditional shamanic rituals) will be used. They were designed and previously employed by one of the authors (CS), who is the first Westerner to become an *ugdan* (female shaman in Mongolia), and recognized as an international expert on SICT (Sombrun, 2006, 2012). Different kinds of trances will be taught during the workshops: trances with intention, during which participants follow an intention [e.g., refocusing on oneself (“anchor trance”), finding one’s place and being assertive (“territorial trance”), reconnecting with one’s inner power (“power trance”)], and trances without intention (“free trances”), during which participants let themselves and their body get carried away by the experience of trance. During each session, 4–5 SICT exercises will be proposed (see Table 2). Typically, participants will lie down and listen to one of the sound loops (± 30 min). The access to SICT can manifest itself through various elements: vocalizations or movements for examples. Every exercise will be debriefed in group, and a focus on self-compassion will be suggested during the workshops using specific intentions (e.g., an intention to be gentle with oneself, set self-boundaries). At the end of the two workshops, all participants will have found a way to induce SICT without the help of the sound loops. At-home practice will be encouraged during the two  weeks between the workshops and after them.

The three interventions will take place in Liège (hypnosis, SICT) and Brussels (MSC meditation). During the entire study duration, each participant will benefit from usual care, including medical care, oncological revalidation, and individual psychological help if necessary. Although no adverse event has been reported in our previous studies on hypnosis with patients with cancer or chronic pain (Grégoire et al., 2017, 2018b, 2020a; Bicego et al., 2021b) and clinical practice, it could be possible that a patient feels uncomfortable during the exercises. In this case, they will have the possibility to stop the session and their participation in the study. The therapist or the experimenter can also propose a meeting to discuss their difficulties and, if necessary, suggest a meeting with a psychologist or physician with whom we collaborate. Any reason for drop-out will be consigned. Adherence to the study is fostered by the facts that all participants are volunteers and motivated to participate and that the assessments can be mainly done at home and require only three travels to the hospital during the whole study. Several reminders will also be sent to the participants who forget to answer the questionnaires in time and who did not ask to quit the study.

